# Optimizing short-term antibiotic treatment in patients with acute cholangitis: study protocol for an open-label randomized controlled trial (the BOLT-P3 trial)

**DOI:** 10.1186/s13063-025-09077-1

**Published:** 2025-09-01

**Keywords:** Antibiotic stewardship, Cholangitis, Endoscopic retrograde cholangiopancreatography, Antibiotic resistance, Duration of antibiotic therapy, Randomized control trial

## Abstract

**Background:**

Acute cholangitis (AC) frequently presents as a community-acquired infection and is associated with a high prevalence of antibiotic use among infectious diseases. The Tokyo Guidelines 2018 (TG18) recommend 4–7 days of antibiotic administration after biliary drainage. However, this recommendation lacks strong evidence of its effectiveness and is primarily based on heterogeneous clinical findings and expert opinions. Recent retrospective studies have advocated a shorter 1- to 3-day antibiotic course as effective for AC treatment, prompting the need to reassess the treatment duration to achieve therapeutic efficacy while minimizing resistance and adverse effects.

**Methods:**

We designed a multicenter, non-blinded, randomized trial to evaluate the efficacy of short-course therapy compared to standard-course therapy for AC management. The short-course therapy group will receive 1–3 days of intravenous (IV) antibiotic treatment after successful biliary drainage compared to 4–7 days of IV antibiotics after successful biliary drainage for the standard-course therapy group. The primary outcome is the clinical cure rate within 14 days from the endoscopic retrograde cholangiopancreatography (ERCP) procedure. Participants will be allocated to either treatment course using a minimization method in a non-blinded, randomized manner, with stratification factors including condition severity and facility. We determined that 210 participants would be required to achieve a statistical power of 90% with a one-sided significance threshold of 2.5% and a non-inferiority limit of 10%.

**Discussion:**

This phase 3 trial aims to determine the non-inferiority of short-course therapy over standard-course therapy. Shortening the duration of antibiotic administration may mitigate the emergence of resistant bacteria, adverse events, and reduce hospital stay length and healthcare costs.

https://jrct.niph.go.jp/re/reports/detail/73862

**Trial registration:**

This study was registered at the Japan Registry of Clinical Trials under registry number jRCT1031230709. Registered on 14 March 2024, https://jrct.niph.go.jp/re/reports/detail/73862

**Supplementary Information:**

The online version contains supplementary material available at 10.1186/s13063-025-09077-1.

## Background

The risk of developing resistant organisms increases with each additional day of antimicrobial therapy (1). Furthermore, prolonged antibiotic use has been reported to increase healthcare costs; escalate adverse events associated with antimicrobial therapy—such as *Clostridioides difficile* enteritis, invasive candidiasis, antibiotic-induced organ damage; and increase mortality rates in certain infections, including intra-abdominal infections (1–7). Therefore, optimizing antibiotic use in acute cholangitis (AC), which ranks as the second or fourth most prevalent cause of community-acquired bacteremia (8,9), is crucial for suppressing resistant bacteria and reducing antibiotic-associated adverse events (10).

The Tokyo Guidelines 2018 (TG18), a well-recognized set of guidelines for AC management, recommend antibiotic therapy and biliary drainage as the primary treatment modalities. TG18 suggests a standard duration of 4–7 days for antibiotic administration post-biliary drainage (11). However, it is noted that a duration of ≤ 3 days of antimicrobial therapy may suppress the development of resistant organisms (12).

A recent randomized controlled trial (RCT) compared 4- and 8-day antibiotic treatment durations and confirmed the non-inferiority of the shorter regimen (13). Additionally, recent retrospective studies have suggested that an even shorter course of antibiotics, lasting 1–3 days post-biliary drainage, may be effective in treating AC (14–16). These studies indicate that reducing the duration of antibiotic therapy does not compromise the clinical cure rate and may mitigate the risks associated with prolonged antibiotic use, including the development of resistant organisms and other adverse effects.

Despite the growing body of evidence, recommendations are predominantly based on small retrospective studies. Therefore, obtaining more robust evidence to refine and validate the optimal antibiotic therapy duration for AC is imperative to ensure maximal therapeutic benefit while minimizing adverse effects. This study aims to evaluate whether short-course therapy is non-inferior to standard-course therapy in terms of clinical cure rate. The research is crucial for developing evidence-based guidelines that balance the efficacy of treating AC with the need to prevent the emergence of resistant bacteria and reduce antibiotic-related adverse events.

## Methods

### Design

We aim to conduct a multicenter, open-label, randomized trial to assess the non-inferiority of short-course therapy compared with standard-course therapy for AC management after successful biliary drainage. A comprehensive report of the trial will be prepared in accordance with the Consolidated Standards of Reporting Trials (CONSORT) guidelines, including specific recommendations for non-inferiority studies (17). This study was registered with the jRCT under the identifier jRCT1031230709. The protocol of this study was developed according to the Standard Protocol Items Recommendations for Interventional Trials (SPIRIT) guidelines, with the SPIRIT checklist included as Additional file. A detailed diagram of the methodology used in this study is shown in Fig. 1.

**Fig. 1 Fig1:**
[figure not shown]
Study methodology

### Research implementation period

The study will be conducted from the date of the facility director’s approval until March 31, 2027, and includes the following phases: an enrollment period until March 31, 2026; a follow-up period until April 30, 2026; and a final phase for manuscript writing, academic presentations, and reporting from April 30, 2026, to March 31, 2027.

### Patients

Patients who meet the diagnostic criteria for confirmed or suspected AC according to the TG18 will be considered eligible for trial participation (18). Patients will be enrolled in the study when both the attending physician and the patient consent to participate in the trial, and the participant fulfills all eligibility criteria without meeting any exclusion criteria.

### Exclusion criteria

Participants will be excluded if they meet any of the following criteria:
Circulatory insufficiency with catecholamines at the time of ERCP.Requiring intensive care unit (ICU) admission.Hypothermia (35).Recurrent cholangitis within three months.Malignant or benign biliary stricture being equivalent to or beyond the Bismuth type II in the hepatic portal area or having an indeterminate cause of biliary obstruction (20).Having anatomical changes due to surgery (e.g., biliary jejunal anastomosis excluding Billroth I).Being diagnosed with concomitant pancreatitis based on the International Pancreatic Society/American Pancreatic Association guidelines (meeting two of the following criteria) (21): upper abdominal pain, serum amylase or lipase >3x upper limit of normal (ULN), and imaging signs of acute pancreatitis.Concurrent cholecystitis according to the TG18 criteria (meeting one item from A and one from B and C):Concurrent hepatic abscess.Concurrent other infections.Receiving continuous antibiotic administration for more than one week before registration.Having complications from ERCP before registration (perforation; pancreatitis; bleeding; cholecystitis; or cardiopulmonary diseases due to sedation, e.g., aspiration, pneumonia, choking, and cardiac arrest, among others (26–28)).Specific immunosuppressed states:Being pregnant.Being excluded from participation in the trial by the attending physician for other reasons.

### Ethics and informed consent

This trial will adhere to the ethical standards outlined in the Declaration of Helsinki and the guidelines for medical and health research involving human participants issued by Japan’s Ministry of Health, Labour and Welfare and Ministry of Education, Culture, Sports, Science and Technology (29). The ethical review boards of all involved hospitals approved the study protocol. Written informed consent was obtained from all participating patients and their legal proxies.

### Randomization and allocation concealment

Participants in the study will be assigned to one of the treatment groups in a balanced 1:1 ratio within 24 h of the successful completion of biliary drainage. The allocation process will utilize a stochastic minimization method centrally managed by the study’s primary center at the Department of Gastroenterology, Shonan Kamakura General Hospital. A specialized electronic data capture system will be used for randomization and data collection. Stratification factors will include condition severity and facility as criteria.

### Trial interventions

This study will compare short-course (1–3 days) and traditional standard-course (4–7 days) antibiotic therapy for AC management after successful biliary drainage.

The antibiotics administered to study participants are commercially available and approved for use in Japan. They will be administered at the standard dosage specified in the package insert. The initial antibiotics will be selected at the discretion of the treating physician. The selected antibiotics can be changed to other antibiotics during treatment based on culture/susceptibility test results or any suspected or occurring adverse reactions in the patient. Adjustments based on patient renal function or other criteria will be performed when judged appropriate and necessary by the attending physician.

### Extension of the antibiotic administration period

Extending the treatment period in AC is not mandatory, even with positive blood culture results. Several retrospective studies have shown that short-term administration of antibiotics (2–3 days) does not worsen outcomes, even in cases with positive blood cultures (16,30). In response, the Société de Pathologie Infectieuse de Langue Française (SPILF) recommends a short-term antibiotic administration period (within 3 days), even for cholangitis with bacteremia (31). However, an extension of the antibiotic administration period is permissible and recommended at the discretion of the attending physician in cases that meet any of the following criteria:Antibiotics were administered for over 72 h during the short-course therapy until the blood culture sensitivity results were known.For blood cultures positive for *Staphylococcus*, antibiotic therapy for more than 14 days is recommended, followed by a confirmatory negative blood culture (32).Recommending a change of antibiotics if the blood culture sensitivity results show that the antibiotic spectrum is inappropriate to cover the infection. The duration of treatment after changing antibiotics will be 24–72 h for the short-course therapy group and 96–168 h for the standard-course therapy group.Allowing a change or extension of antibiotics with a lack of improvement in clinical symptoms (chills, body temperature > 37.5 °C on the third day of enrollment (33), abdominal pain, or jaundice). However, antibiotic administration should be limited to a maximum of 7 days.Even if antibiotics are discontinued once, it is permissible to restart them in cases of poor drainage (if the T-bilirubin level on the third day after ERCP abnormally exceeds 80% of the level before ERCP (34)). However, antibiotic administration should be limited to a maximum of 7 days.Extending the antibiotic administration period up to 14 days, including oral administration, is permissible at the discretion of the attending physician in patients already diagnosed with artificial valve replacement surgery, previous infectious endocarditis, or congenital heart disease (single ventricle, complete transposition of the great vessels, tetralogy of Fallot) or if gram-positive coccal bacteremia is confirmed.Extending the antibiotic administration period according to concurrent infection is recommended if other infections, such as liver abscess, cholecystitis, or intra-abdominal abscess, are discovered after starting the trial. Cholecystitis and intra-abdominal abscesses should be treated for 1–4 days after appropriate source control (35–37). Evidence regarding liver abscess treatment is scarce; nevertheless, the duration of antibiotic treatment should be tailored to the patient’s condition, ranging from 8 to 69 days (38). Recommending an appropriate antibiotic administration period in cases where the source of infection cannot be controlled is difficult; nevertheless, the general recommendation is 1–2 weeks for cholecystitis and 2–6 weeks for liver abscesses.

### Assessment and follow-up

The schedule of assessments is shown in Fig. 2. Clinical assessments will be performed on the date of the ERCP procedure, the day after ERCP, at the end of antibiotic administration, and on days 14 and 30 after ERCP.

**Fig. 2 Fig2:**
[figure not shown]
Schedule of assessments. *1: Hematological tests, including white blood cells, white blood cell differential, red blood cells, hemoglobin, hematocrit value, and platelets. *2: Blood biochemistry tests, including creatinine, total bilirubin, direct bilirubin, aspartate aminotransferase, alanine aminotransferase, alkaline phosphatase, gamma-glutamyl transferase, C-reactive protein, and amylase. *3: Adverse events, including rash, diarrhea, *Clostridioides difficile* enteritis, liver damage, and kidney damage. *4: In this trial, blood cultures were collected within 24 h of initial contact with the treating physician before the start of antibiotic administration. *5: Endoscopic retrograde cholangiopancreatography (ERCP) procedure details (stone removal, plastic stent, metallic stent, and balloon dilation, among others) and adverse events (bleeding, perforation, pancreatitis, bile leak, cholangitis, or liver abscess)

In this trial, direct follow-up by the principal investigator and sub-investigators is the primary approach. For participants who miss follow-up visits, efforts will be made to collect data via telephone contact whenever possible.

### Outcome measures

The primary outcome was defined as the rate of cases that achieved clinical cure within 14 days and survived without recurrence, according to the guidelines recommended by the U.S. Food and Drug Administration for complicated urinary tract infection outcomes (39). Clinical cure refers to the resolution of all pre-treatment clinical symptoms (chills, fever > 37.5 °C, abdominal pain, jaundice, impaired consciousness). Recurrence was defined as the reappearance of clinical signs suggestive of cholangitis in a case that had completed antibiotic therapy and achieved clinical cure, necessitating the resumption of antibiotic administration. Clinical signs suggestive of cholangitis recurrence include any of the following: (1) reappearance of clinical signs of cholangitis; (2) manifestation of signs of infection in the liver, pancreas, or biliary tract; or (3) other signs of infection considered related to the initial cholangitis episode (30,40).

The secondary outcomes include the following:Recurrence rate within 30 daysMortality rate within 30 daysTotal number of days of antibiotics required for both groups within 30 daysTotal number of days of hospitalization required for both groups within 30 daysClinical cure rates by severityClinical cure rates by the presence or absence of fever at the end of antibiotic treatmentClinical cure rates in older populations aged ≥ 75 years (18,41)Clinical cure rates by blood culture resultsClinical cure rates by bile culture resultsClinical cure rates based on antibiotic susceptibility before ERCPClinical cure rates based on antibiotic administration duration before ERCPClinical cure rates based on the time from admission to the ERCP procedureClinical cure rates based on AC etiologyTreatment costsIncidence of the following adverse events within 14 days:(a). Rash(b). Diarrhea (defined as ≥ 3 loose stools per day (42))(c). *C. difficile* enteritis (42), confirmed experimentally and through clinical signs

Clinical signs: Presence of diarrhea (≥ 3 formless stools within 24 h).

Experimental confirmation:Detection of *C. difficile* toxin A and/or toxin B in stoolPositive *C. difficile* stool antigenPositive *C. difficile* cultureDetection of specific genes of *C. difficile* by molecular diagnostic methods such as polymerase chain reactionDetection of *C. difficile toxins *by the cell cytotoxicity neutralization assayDrug-induced liver injury (43), according to any of the following criteria:Hepatic dysfunction (alanine aminotransferase [ALT] elevation exceeding 5 × ULN)Alkaline phosphatase (ALP) elevation exceeding 2 × ULNALT elevation exceeding 3 × ULN, and total bilirubin concentration exceeding 2 × ULN

Additionally, drug-induced liver injury will be diagnosed if there is no observed worsening of biliary duct dilation upon re-evaluation with imaging diagnostics, or if there is a re-elevation of hepatic and biliary enzymes following an initial decrease.Acute kidney injury (44), according to any of the following criteria:An increase in serum creatinine by ≥ 0.3 mg/dL (≥ 26.5 µmol/L) within 48 h from the time of initial administration of antibiotics at the start of the trial (or from the time they were first used, if before the start of the trial)An increase in serum creatinine to ≥ 1.5 times the baseline from the time of initial administration of antibiotics at the start of the trial until the end of administration

Serum creatinine results obtained by the attending physician within this period will be included in the evaluation, even if measured on non-scheduled test days.

The baseline during normal times was defined as the creatinine value within 1 year before the start of the trial. In cases with an unknown baseline, the lowest value within 7 days before the end of antibiotic administration will be used as the baseline.

Adverse events will be graded using the Common Terminology Criteria for Adverse Events version 5.0 (45).

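### Recurrence counts only after a completed antibiotic course, so whether a new infection by day 14 is a primary-outcome failure depends on the randomised duration

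*Protocol article*

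**What the plan says.** Under Outcome measures, the primary outcome is "the rate of cases that achieved clinical cure within 14 days and survived without recurrence". It has three components.

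- **Cure:** "Clinical cure refers to the resolution of all pre-treatment clinical symptoms", with chills, fever above 37.5 °C, abdominal pain, jaundice and impaired consciousness listed. New symptoms and repeat drainage are not mentioned.
- **Survival.**
- **No recurrence:** signs suggestive of cholangitis count only "in a case that had completed antibiotic therapy and achieved clinical cure, necessitating the resumption of antibiotic administration". Besides returning signs of cholangitis, the qualifying signs include "manifestation of signs of infection in the liver, pancreas, or biliary tract" and "other signs of infection considered related to the initial cholangitis episode". Neither of these two has to have been present before treatment.

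The section on extension of the antibiotic period provides for events during or just after the course:

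- "Allowing a change or extension of antibiotics with a lack of improvement in clinical symptoms";
- "Even if antibiotics are discontinued once, it is permissible to restart them in cases of poor drainage", with a bilirubin trigger on the third day after ERCP;
- longer treatment when liver abscess, cholecystitis or intra-abdominal abscess is found after the trial has started. The Discussion repeats this for patients who develop these conditions after registration.

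Outcome measures does not say how any of these count. Statistical analysis gives the arms as 24–72 h and 96–168 h. The Discussion states that attending physicians assess the outcome in this open-label trial and relies on clear definitions to limit subjectivity.

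**The concern.** A trial of treatment duration needs a failure definition that works the same way whether or not treatment is still running. Here the recurrence component becomes available only once antibiotics have stopped, and the stopping time is what is randomised. Before that point only the cure component can register a failure, and it looks back to the symptoms at admission.

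The protocol itself expects new infections after registration and provides for extended courses, so the uncovered cases are foreseeable. At stake is a non-inferiority conclusion that rests on very few failures, classified by unblinded physicians under a rule that treats the arms differently.

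**Working it through.** **1. The same event under the written rule.** Take two patients whose admission symptoms have resolved by day 3 after ERCP. Both develop cholecystitis on day 5 and are alive and free of their admission symptoms at day 14.

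| | Short arm (antibiotics ended by 72 h) | Standard arm (course running to 168 h) |
|---|---|---|
| Course completed before the event? | Yes | No |
| Cure reached before the event? | Yes | Yes |
| Antibiotics resumed? | Yes, restarted | No, course continued or extended |
| Recurrence? | Yes | No |
| Primary outcome | Failure | Success |

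**2. Which cases remain uncounted.** If the admission symptoms resolve by day 14, these are not failures as written:

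- new infection, or repeat drainage for infection, while the first course is running;
- the same during an extended course. The article cites liver-abscess courses of 8 to 69 days, so the completed-course condition may not be met by day 14;
- new signs of infection, or repeat drainage, handled without resumed antibiotics.

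A restart for poor drainage on bilirubin alone is left unclassified.

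**3. The plan's own sample size.** Inputs from Sample size: cure 95% in both arms, margin 10 points, one-sided 2.5%, power 90%.

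n per arm = (z₀.₉₇₅ + z₀.₉₀)² × 2 × 0.95 × 0.05 / 0.10² = 10.507 × 0.095 / 0.01 = 99.8, so 100 per arm and 200 in total. This matches the article. Expected failures at full enrolment: 210 × 0.05 = 10.5.

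**4. How far one patient moves the result.** The article names no interval method, so a Wald 95% interval is assumed here. With 105 per arm, the upper limit for the excess of short-arm failures is d + 1.96 × √[(p₁(1−p₁) + p₂(1−p₂))/105].

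| Failures, short v standard | d | SE | Upper limit | Below 10%? |
|---|---|---|---|---|
| 8 v 5 | 2.86% | 3.32% | 9.4% | Yes |
| 9 v 5 | 3.81% | 3.43% | 10.5% | No |
| 8 v 4 | 3.81% | 3.19% | 10.1% | No |

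Leaving one short-arm failure uncounted (9 to 8, against 5) turns a negative result positive. Leaving one standard-arm failure uncounted (5 to 4, against 8) turns a positive result negative.

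**5. Direction under two opposite assumptions, 100 per arm.** The documents give no rate of uncounted failures, so both are illustrations only.

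- *Equal share missed in both arms, true cure 95% v 85% (at the margin).* With a share f missed, observed cure is 1 − 0.05(1−f) v 1 − 0.15(1−f). By exact enumeration with the Wald interval, the chance of declaring non-inferiority is 3.4% at f = 0, 5.8% at 10%, 9.6% at 20% and 15.7% at 30%.
- *One fifth missed in the standard arm only, true cure 95% in both.* Observed cure is 96% v 95%. SE = √[(0.95 × 0.05 + 0.96 × 0.04)/100] = 0.0293, and power = Φ((0.10 − 0.01)/0.0293 − 1.96) = 86.7%, against 90.05% with none missed.

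The first pattern favours non-inferiority and the second works against it.

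**The case against.** **The composite covers much of the ground.** A reader might infer from the cure sentence that any patient with new fever, chills or confusion at day 14, or any patient re-drained for infection, is scored a success. The documents do not support that. Success also requires survival without recurrence, and two of the three recurrence signs include infection that was absent at admission. Extension for non-improvement and restart for poor drainage are both capped at 7 days, and longer courses are confined to listed exceptions. Most patients will have finished well before day 14, so a biliary infection then treated with antibiotics is usually a failure already. This stands, and it confines the defect to the cases in step 2.

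**The direction is not established.** A reader might also infer that missed failures pull the arms together and favour non-inferiority. The short arm becomes eligible for recurrence several days before the standard arm, which can work the other way. This stands as well.

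**The fragility is generic.** The limits in step 4 would look the same for any endpoint in a trial of this size. They show why classification matters here, not how often it goes wrong.

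**The article is condensed.** The full protocol may say how extended or restarted courses count. That is possible, but the article states the cure and recurrence definitions with their conditions, and it is those stated conditions that differ by arm.

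**Changing a primary endpoint during recruitment has a price.** Recruitment began in June 2024, and the 95% assumption belongs to the present endpoint. This stands and is costed under the fix.

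**Conclusion.** The point holds in a limited form. The primary-outcome definition ties recurrence to a completed course followed by resumed antibiotics, and ties cure to admission symptoms. New infection or repeat drainage for infection during a running or extended course, or handled without resumed antibiotics, can therefore be scored a success. Because the length of the course is randomised, failure is ascertained differently in the two arms, in an open-label trial with outcomes judged by attending physicians.

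Neither the frequency of such cases nor the net direction of the bias follows from the documents. No figure in the sample-size section is wrong on this account. With about 10 failures expected, one or two reclassified patients could decide the result, on the assumption of a Wald interval and counts near those in step 4. The wording should be corrected before analysis.

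**What to change.** Before analysis, amend Outcome measures as follows.

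- Define primary-outcome failure to include any new or recurrent sign of biliary or related infection, or unplanned repeat biliary drainage for infection, from randomisation to day 14. This should apply whether or not the course had been completed or antibiotics were resumed.
- State how each kind of extended or restarted course allowed in the extension section counts.
- Apply the rule identically to both arms from recorded data.
- Report the definition as now written as a sensitivity analysis.

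No treatment rule changes. A day-14 assessment is already scheduled. The Fig. 2 legend lists ERCP "procedure details (stone removal, plastic stent, metallic stent, and balloon dilation, among others" and ERCP adverse events including cholangitis and liver abscess, but does not mention repeat drainage, so it should be confirmed that repeat procedures up to day 14 are captured. An Event Adjudication Committee is listed in Table 2 without a described role; if it is to classify these events, the protocol should say so.

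The cost is a re-check of records and a somewhat lower cure rate. With power = Φ(0.10/√[2p(1−p)/100] − 1.96) at 100 per arm:

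| Assumed cure, both arms | Power at 100 per arm | Total analysed for 90% power |
|---|---|---|
| 95% (plan) | 90.05% | 200 |
| 94% | 84.6% | 238 |
| 93% | 79.1% | 274 |

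The rates below 95% are assumptions.
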